### Recruitment

Posters will be placed in the therapies out-patient department to increase awareness of the study, and flyers will be sent out with first appointment letters. Healthcare professionals will be briefed on the participant eligibility criteria and will introduce the study to potential participants during their first appointments. If potential participants express an interest during this appointment, they will then be introduced to a member of the research team (after their appointment). The researcher will provide verbal and written information about the trial on the same day (Fig. 1).

All interested patients will be given a minimum of 24 h to consider their participation in the study, to allow them time to read the trial literature, formulate questions and discuss their participation with relevant others. A member of the research team will call or email these potential participants. Interested patients who decline participation in the study at this stage will be asked to briefly provide the reasons for their decision; however, they will not be obliged to provide a reason if they do not wish to. Permission will also be sought to obtain demographic data such as age, ethnicity and gender from any patients who are approached but decline participation. This information will be used to characterise the sample and will inform recruitment strategies for a future multicentre trial. Participants will be free to withdraw at any point during the study without needing to provide a reason. Data will be retained for all participants up to the date of withdrawal.

### Screening and enrolment

Written informed consent will be obtained from all patients who agree to participate in the trial. This will be obtained during routine musculoskeletal appointments within 3 weeks after first being approached. After obtaining informed consent the research team will complete a screening process with the participant to ensure they meet the study inclusion and exclusion criteria. This will include asking them to fill in the PHQ-ADS questionnaire. If excluded from the trial, the participant will be informed of the reason.

### Randomisation and allocation

The study will follow the Consolidated Standards of Reporting Trials (CONSORT) guidelines^23^ for the design and implementation of randomised controlled trials. The CONSORT extension for randomised pilot and feasibility trials is meant to provide reporting guidance for any randomised study in which a future definitive RCT, or part of it, is conducted on a smaller scale. After the consent and eligibility procedure, participants will be randomised in a 1:1 ratio (collaborative care:usual care). Allocations will be concealed and undertaken using online randomisation software^24^ by a member of the research team. Since this study aims to assess the feasibility of the CCM, which includes support from a case manager, it will not be possible to mask healthcare professionals or participants to the intervention.

### Data collection methods

#### Baseline assessments

After randomisation, participants from the intervention and control arms will be asked to complete baseline questionnaires, lasting approximately 60 min. These will include tailored questionnaires to collect demographic data (age, gender, ethnicity, marital status, highest qualification level and employment status), medical history and current medication usage. All participants will also be asked to complete other patient-reported outcome measures at baseline, including self-reported measures of depression, anxiety, pain and quality of life (see the ‘Patient-reported outcomes’ subsection above).

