## Method

This will be a mixed-methods, unmasked (unblinded), parallel-group RCT. This protocol was written with reference to the Standard Protocol Items: Recommendations for Interventional Trials (SPIRIT) checklist.^16^

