#### Quantitative data

Owing to the exploratory nature of this feasibility study, the sample size will be based on the pragmatic limits of recruitment. Since the primary aim of this study is to determine the feasibility of conducting a future RCT, a descriptive analysis will be performed to examine key feasibility and process-related outcomes. All quantitative data will be uploaded into SPSS^27^ for analysis, where recruitment, retention and follow-up rates at study completion will be quantified using absolute and relative frequencies and percentages of the overall population.

In particular, the percentage of potential participants who agree to undergo the screening assessment out of the total number of potential participants who were initially invited will be calculated. The percentage of the total number of participants who were enrolled into the study out of the total number invited will be calculated with a 95% confidence interval ±6%.

The main analysis will estimate the percentage of potentially eligible participants, consent and overall uptake. The retention, follow-up and outcomes rates will be calculated in relation to the number recruited. Engagement with the intervention will be described by the percentage of appointments attended as a proportion of booked appointments. An estimated engagement rate of approximately 90% (32/36 retained patients) will give a 95% confidence interval width of ±10%. Additional healthcare resources will be described by type and frequency of use in absolute numbers.

The means and confidence intervals of clinical outcomes will be calculated to determine their sensitivity to change. This will guide the identification of a primary outcome measure for a future RCT. In addition, we will determine the acceptability of the clinical outcomes by calculating percentage rates of completion for the PHQ-ADS, EQ-5D-3L, NPRS, PDI, MSK-HQ and the GRoC.

A detailed statistical analysis plan will be developed by the study statistician. To illustrate participant flow, we will report results using a CONSORT flow diagram.^23^

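### The self-report baseline battery follows randomisation in an unmasked trial, so four outcome scales have no described pre-allocation measurement

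*Protocol article*

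**What the plan says.** The order of events is set across three consecutive parts of the protocol article. Under Screening and enrolment, patients consent and are then checked for eligibility. Of that check the article says: "This will include asking them to fill in the PHQ-ADS questionnaire". Under Randomisation and allocation, 1:1 randomisation follows consent and eligibility. Under Baseline assessments the article then says: "After randomisation, participants from the intervention and control arms will be asked to complete baseline questionnaires, lasting approximately 60 min". The battery covers demographics, medical history and medication, and patient-reported measures, "including self-reported measures of depression, anxiety, pain and quality of life".

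On masking, the Method section says: "This will be a mixed-methods, unmasked (unblinded), parallel-group RCT". Randomisation and allocation adds that "it will not be possible to mask healthcare professionals or participants to the intervention".

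The scores have two stated uses under Quantitative data. The first is: "The means and confidence intervals of clinical outcomes will be calculated to determine their sensitivity to change". The article adds that this will guide the choice of primary outcome for a later trial. The second is to judge the acceptability of the measures by "calculating percentage rates of completion for the PHQ-ADS, EQ-5D-3L, NPRS, PDI, MSK-HQ and the GRoC".

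**The concern.** A baseline value is useful because the allocated arm cannot have influenced it. Here, on the order described, participants may already know whether they have a case manager when they rate pain, disability and quality of life. A patient pleased or disappointed by the allocation may answer differently, or may not finish an hour of questionnaires.

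The arms also differ in what the answers are for. Under Interventions, the case manager tracks progress each month with the questionnaires first given at baseline and adjusts support accordingly. Only intervention participants have baseline answers that feed into their care in this way.

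Two deliverables are at stake: the description of how far each scale moves from baseline, and the baseline completion and missing-data rates, which the article lists among its feasibility indicators.

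**Working it through.** **1. Order of procedures, scale by scale**

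| Scale | Before randomisation | After randomisation |
|---|---|---|
| PHQ-ADS | Yes, at screening | Depression and anxiety measures listed in the battery |
| EQ-5D-3L, MSK-HQ, NPRS, PDI | None described | Yes, in the battery |

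GRoC is left out because it rates change and a pre-allocation value has little meaning. Nothing in the text places the four scales earlier or delays disclosure of the allocation. For PHQ-ADS, the article does not say which of the two administrations is the baseline.

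**2. Effect on mean change (illustration)**

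The documents give no size for an allocation-driven shift, so d is an assumption. Let an arm's true mean change be M6 − M0, and let knowledge of the allocation move its recorded baseline to M0 + d, with follow-up unaffected. Then:

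recorded change = M6 − (M0 + d) = (M6 − M0) − d

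The bias in that arm's mean change has size d. For assumed shifts of 0.1, 0.2, 0.3 and 0.5 SD it is 0.1, 0.2, 0.3 and 0.5 SD. If change is described over both equal arms together and only one arm shifts, the bias is d/2, that is 0.05 to 0.25 SD over the same range. If the shift persists unchanged to 6 months, it cancels and the bias in change is zero.

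**3. Would the data reveal it?**

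With 20 per arm, the standard error of a difference between two baseline means is √(1/20 + 1/20) = √(2/20) = 0.32 SD. An assumed shift of 0.2 SD is less than one standard error, so a baseline table could not distinguish it from chance imbalance.

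**4. Effect on completion**

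One missing form is 1/20 = 5 percentage points of an arm and 1/40 = 2.5 points overall. Two missing forms in one arm lower its completion to 18/20 = 90%.

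**5. Does moving the battery disturb the plan's stated precision?**

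- Recruitment rate (Sample size): 1.96 × √(0.20 × 0.80 / 200) = 0.055, which rounds to the stated ±6%.
- Engagement (Quantitative data): 1.96 × √(0.90 × 0.10 / 36) = 0.098, or 0.103 at exactly 32/36. Both agree with the stated ±10%.

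Both figures are reproduced, and neither depends on when the battery is given.

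**The case against.** The strongest reply is that this is a 40-patient feasibility study with descriptive analyses and no hypothesis testing, so there is no treatment-effect estimate to bias. That largely stands, and it rules out several stronger readings that a reader might infer.

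- **All baseline patient-reported outcomes are contaminated.** Not supported. PHQ-ADS, the anxiety and depression measure, is completed at screening before randomisation. Demographics and medical history in the battery are unlikely to depend on allocation.
- **The between-arm difference in change, or a baseline-adjusted difference, will be biased by a stated amount.** The article plans neither a between-arm contrast nor an adjusted model. Any such figure would describe an analysis that is not planned, and would need the further assumption that follow-up, also self-reported and unmasked, is unaffected by allocation.
- **The co-primary outcomes are compromised.** Participation and recruitment turn on willingness and consent, which precede allocation. Loss after allocation would not be hidden: retention after randomisation is recorded, rates use the number recruited as denominator, and a CONSORT diagram is planned. Uneven early loss would be a correct description of the procedure as run.
- **The definitive trial will inherit the order.** Nothing commits it to do so. The Discussion expects refinements and suggests that cluster randomisation be considered.

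It can also be said that being randomised is not the same as being told. The article does not state when participants learn their allocation, and the flow diagram (Fig. 1) could not be consulted for this check. But nothing in the text indicates delayed disclosure. If disclosure is delayed, the article should say so.

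What the reply does not answer is the sensitivity-to-change assessment. It is a planned use of the scores, it depends on a sound baseline, and four scales have no described pre-allocation value.

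**Conclusion.** The point holds in a limited form. The article places the self-report battery after randomisation in a trial whose participants cannot be masked, without saying that allocation is withheld. EQ-5D-3L, MSK-HQ, NPRS and PDI lack a described pre-allocation measurement; PHQ-ADS has one that is not designated as baseline.

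The documents support saying that scores and completion can be altered, not that they will be. The size is unknown: bias in one arm's mean change equals whatever baseline shift occurs, provided that follow-up is unaffected. Each missing form costs 5 points of an arm's completion.

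The weakness falls on a secondary, descriptive part of the study and leaves participation and recruitment untouched. It should be fixed because the remedy is cheap and later analysis cannot recover a missing pre-allocation score, but it does not threaten the main feasibility conclusions.

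**What to change.** In Baseline assessments, change the timing so that the questionnaires are completed after consent and eligibility screening and before randomisation. Alternatively, keep the order and state that the allocation is withheld from participants and from staff in contact with them until the battery is complete. In either case, name the pre-randomisation PHQ-ADS as the baseline score for that scale.

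The cost is a change of visit order and a minor amendment. An occasional eligible patient will spend about an hour on the battery and then not be randomised; that loss would be counted before randomisation instead of after it. Because entry requires a PHQ-ADS score of at least 20, change measured from the screening score may include some regression to the mean in both arms, and the report should say so. The sample size and the stated ±6% and ±10% precision are unchanged.

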#### Follow-up assessments

Participants from the intervention and control arms will be invited to complete the same patient-reported outcome measures at follow-up assessments that were completed at baseline, i.e. self-reported measures of depression, anxiety, pain and quality of life (further detailed below). They will also be asked to provide details about any changes to their medication usage. The use of additional healthcare resources will only be recorded at 6 months. All data will be collected through questionnaires administered during face-to-face appointments and telephone or video calls, depending on participant preference and availability.

#### Embedded qualitative study: acceptability of the intervention and facilitators and barriers to implementing the CCM

Focus groups and interviews will be used to explore the views, thoughts and experiences of both participants and healthcare professionals from the intervention group. This will include exploring opinions on working with a case manager, potential advantages of the CCM, and challenges to delivering and receiving the intervention.

##### Interviews

Participants allocated to the intervention group will have the option of taking part in an interview within a month of completing the 6-month follow-up. This interview will last for approximately 60 min, with some guided topics delivered by a member of the research team. Participants can decline to take part at any point. All interviews will be planned to take place in person at the hospital. However, in the event of any COVID-19 or similar restrictions or participant preference, there will also be the opportunity to participate in interviews using a virtual platform or via telephone. Interviews will avoid breaches of confidential material regarding participants’ mental health conditions.^25^ All interviews will be audio-recorded and consent will be obtained before recording.

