**Method:**

A two-arm parallel-group randomised controlled trial will recruit 40 adult out-patients with at least moderate anxiety and depression, who have been referred for physiotherapy and occupational therapy. Participants will be allocated on a 1:1 ratio to collaborative care or to usual care. Co-primary outcomes will be key feasibility indicators collected at baseline and at 6 months. A qualitative study will be conducted post-intervention to explore the acceptability and potential improvements to the collaborative care model.

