### Sample size

As this study is a feasibility trial, all analyses will be descriptive, with no hypothesis testing. Consequently, no formal sample size calculation has been conducted. We aim to recruit 40 patients in total, with 20 randomised to each arm.

The study aims to recruit these patients over 3 months, with a target recruitment rate of 20% of all eligible patients. It is estimated that there may be at least 200 new eligible patients in 3 months. Assuming this number of eligible patients, the recruitment rate could be estimated within ±6% with a 95% confidence level.

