##### Focus group

All healthcare professionals (physiotherapists, occupational therapists, psychologists and psychiatrists) who were involved in the care of patients allocated to the intervention arm will be invited to take part in a focus group within 4 weeks of the end of the trial. We aim to invite 6–10 healthcare professionals for the focus group,^26^ which will last approximately 60 min. Focus groups will take place at the hospital and several potential dates will be offered so those invited will have the opportunity to attend the one most convenient to them. Although our preference will be to conduct focus groups in person, they might also be conducted virtually through an online platform in light of any COVID-19 or similar restrictions. We do not expect staff to attend more than one session, but they would be welcome to attend another session if they have additional feedback to contribute.

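### The only patient interview window opens when the 6-month follow-up is completed, so collaborative care participants who leave the trial earlier have no planned interview

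*Protocol article*

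**What the plan says.** The Interviews section fixes both the population and the timing of the patient interviews: "Participants allocated to the intervention group will have the option of taking part in an interview within a month of completing the 6-month follow-up". The abstract agrees on timing: "A qualitative study will be conducted post-intervention to explore the acceptability and potential improvements to the collaborative care model". The section on suicidal thoughts before randomisation, during usual care or at the end-of-study interviews also treats the interview as an end-of-study event.

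On leaving the trial, the Recruitment section says: "Participants will be free to withdraw at any point during the study without needing to provide a reason". It adds: "Data will be retained for all participants up to the date of withdrawal". The same section does seek reasons, but from a different group, those who say no before enrolment: "Interested patients who decline participation in the study at this stage will be asked to briefly provide the reasons for their decision".

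The Primary and secondary outcomes section lists qualitative acceptability to patients and staff, with barriers and facilitators, as a secondary outcome. The Qualitative data section relies on the interviews and focus groups to supply it.

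**The concern.** Completing the 6-month follow-up is the trigger for the interview. A CCM participant who withdraws at month 2, or who cannot be reached at month 6, never meets it, and the article describes no exit interview, no invitation at withdrawal and no attempt after lost contact. If the plan is followed as written, every patient interviewed will have stayed to the end.

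That matters because acceptability is part of the stated aim and the Discussion wants to identify refinements before a definitive trial. People who leave may do so for reasons tied to the intervention or to the burden of the study, and a completers-only sample is weakest on exactly those barriers. The plan would hold reasons from some patients who never received the CCM, and would have no planned way to obtain them from patients who received it and then left.

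**Working it through.** **Step 1: who has an interview window.** Reading the sections together:

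| CCM participant | Completes 6-month follow-up? | Interview window? |
|---|---|---|
| Uses the CCM and stays in the trial | Yes | Yes |
| Stops using the CCM, stays in the trial | Yes (telephone or video allowed under Follow-up assessments) | Yes |
| Withdraws from the trial before 6 months | No | None described |
| Lost, or misses the 6-month follow-up | No | None described |

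The gap is the last two rows.

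**Step 2: inputs for the size.** From Sample size: "We aim to recruit 40 patients in total, with 20 randomised to each arm". From Quantitative data: "An estimated engagement rate of approximately 90% (32/36 retained patients) will give a 95% confidence interval width of ±10" (per cent). The article does not state a retention rate. Setting the 36 retained against the 40 recruited implies 4 lost, or 4/40 = 10%. This is an inference.

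**Step 3: reproduce the plan's own figure.** Half-width = 1.96 × √(p(1 − p)/n).
- p = 32/36, n = 36: 1.96 × √(0.8889 × 0.1111/36) = 0.103, or 10.3 points.
- p = 0.90, n = 36: 1.96 × √(0.90 × 0.10/36) = 0.098, or 9.8 points.

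Both round to the stated ±10%. No figure in the plan is in dispute; the check only confirms that 36 is the denominator the authors used.

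**Step 4: CCM participants without a window.** With balanced losses, 20 × (1 − 36/40) = 2.

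If exactly 4 of 40 are lost at random with respect to arm, the chance that none is in the CCM arm is (20 × 19 × 18 × 17)/(40 × 39 × 38 × 37) = 0.053. The chance of at least one is therefore 0.95.

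**Step 5: range.** The attrition rates below are assumptions. Expected number = 20 × d; chance of at least one = 1 − (1 − d)^20.

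| Assumed CCM attrition d | Expected without a window, of 20 | Chance of at least one |
|---|---|---|
| 5% | 1 | 0.64 |
| 10% | 2 | 0.88 |
| 20% | 4 | 0.99 |
| 30% | 6 | >0.99 |

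**The case against.** The strongest reply is that the Interviews section defines its population by allocation, and the follow-up clause only says when. No sentence excludes leavers. That is right: a reader might infer an explicit exclusion rule, and the text contains none. What stands is the consequence, since the only stated time for the offer is one that leavers do not reach.

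Second, a reader might infer that patients who find the CCM unacceptable go unheard. The documents do not support that. Retention and engagement are separate indicators, and someone who drops the CCM but completes follow-up can be interviewed in person, virtually or by telephone.

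Third, it would be too broad to say that all the acceptability evidence comes from completers. Retention and adherence are co-primary outcomes, rates are calculated on the number recruited, attended appointments are counted against those booked, and the staff focus group may describe difficulties with patients who left. Only leavers' own accounts are missing.

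Fourth, it is tempting to add the 4 of 36 not counted as engaged to the 4 of 40 not retained and call the total the patients with the worst experience. This fails. The 36 spans both arms, the article describes engagement as appointments attended out of those booked, and people leave trials for reasons unrelated to treatment.

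Fifth, the right to withdraw without explanation protects participants and is no fault in the plan.

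Finally, an article may leave sampling details to a fuller protocol. That covers what is unsaid, but the timing clause is stated here.

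**Conclusion.** The point holds as a modest design gap that is cheap to close. As written, the timing clause confines patient interviews to CCM participants who complete the 6-month follow-up, and this probably tilts that source towards a favourable view. The direction is a judgement: it assumes that at least some leavers go for reasons connected with the CCM or the trial.

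The size is about 2 of 20 CCM participants, resting on an inferred retention of 36/40 and losses balanced between arms, or 1 to 6 of 20 over the assumed 5% to 30%. No primary outcome and no stated precision changes. One source for one secondary outcome is affected, but it is the source meant to explain barriers.

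A reader might also infer that the case manager is shut out of the staff evidence, because the Focus group section invites "All healthcare professionals (physiotherapists, occupational therapists, psychologists and psychiatrists) who were involved in the care of patients allocated to the intervention arm" and that list does not name the role. Whether the bracketed list is exhaustive is a matter of reading, and there may be good reason to keep that person out of a group discussing work with a case manager. It is at most a wording clarification.

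**What to change.** Amend the Interviews section so that the offer goes to every participant allocated to CCM. Those who complete the 6-month follow-up keep the present window. Those who withdraw or lose contact are offered a short, optional telephone interview at that point. Seek agreement to this contact at initial consent, and keep the right to decline without a reason. In the results, report how many of those allocated to CCM were and were not interviewed, split by whether they completed follow-up.

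The cost is one line in the consent form, an amended sentence in the protocol, and a few short calls by the existing research team; telephone interviews are already permitted. Some leavers will decline, so the gap will narrow and may not close, which is why reporting who was not interviewed is part of the fix.

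Separately, one phrase in the Focus group section could say whether the bracketed list is complete and how the case manager's account will be collected, if at all.
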